Zoledronic acid is administrated to the patients in order to minimise the risk of PBD. In this study, we want to evaluate if the potential benefit of prolonged zoledronic acid treatment outweigh the increased risk of BON. To minimise the risk of undetected PBD we will from year 2 to 4 conduct regular bone imaging every 3 month. Furthermore, it is mandatory to conduct bone imaging in case of progressive myeloma disease requiring treatment. To further improve the safety of the patients we have invented a less rigours event definition (PDB) compared to the more strict definition (sPBD) where the progression have to be symptomatic to be calculated as an event. All cases of sPBD will be reported annually to the sponsor.

Radiation exposure:

The following text applies to patients in which evaluation of bone disease is conducted with both conventional radiography and low-dose CT, thus it is the patients who receive the highest radiation dose.

Scheduled bone imaging will be conducted seven times during the four years period. Perhaps one extra bone imaging will be conducted in case of relapse from year 2-4. This equals a total radiation dose of 45.5-52 mSv. A patient not included in the study would probably within the same time frame have approximately three conventional radiography and 1-2 low dose CT conducted, equal to a total radiation dose of 11.3-15.4mSv. The patients will over a four years period receive an excess radiation dose of 33.2-36.6, which is equivalent to the dose received from 1.5 conventional CT. The additional bone imaging will not only be conducted for scientific reasons, but also to make sure no serious progressive bone disease occurs when the patient is not receiving zoledronic acid.

Drug administration and renal function

Four mg of zoledronic acid will be administered intravenously at the hospital every fourth week (+/- 1 week) according to local instructions, for either two or four years.

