**1.9 Side Effects.**

Zoledronic acid has been approved by EMEA since 2001 for prevention of SRE in adult patients with advanced malignancies involving the bone. It has been used extensively for many years and has a well-known toxicity profile. It is not financially possible to conduct a new study where all possible side effects will be reported rigorous, as no pharmaceutical companies have shown interest in the study. Furthermore, it is unlikely that new – still unknown – side effects can be identified from this study since all patients most likely will receive multiple lines of anti-myeloma chemotherapeutics that will differ from site to site, and a significant portion of the patients will die due to progressive disease during the protocol. However, the Nordic Myeloma Study Group finds it very relevant to conduct a study with focus on BON, which is a late occurring, severely disabling side effect where the incidence increases proportionally to the exposure time. In this study, we will focus on BON and renal insufficiency as this is a common clinically relevant side effect to zoledronic acid. Patients will furthermore be evaluated using QoL, which ultimately will answer the question whether prolonged treatment with zoledronic acid is of benefit for these severely ill patients. All AEs and SAEs will be documented in the patient’s medical journal but will not be reported in the CRF if they can be related to the myeloma disease or to the chemotherapeutic treatment the patient receives. All SAR and SUSAR will be reported in the CRF. The treating physician decides if an AE or SAE is related to the investigational compound and thus should be reported as an SAR / SUSAR. Summary of Product Characteristics supplied in appendix 5 will be used as reference document to decide if a SAR should be upgraded to a SUSAR. All cases of renal insufficiency, BON, hypo-, and hypercalcaemia, will be reported in the CRF regardless of causality.

Registration of predefined (section 1.9.1 and 1.9.2) AEs, SAEs, SAR, and SUSARs will continue until the last infusions at year 4 +30 days for the treatment group or until year 4 +30 days for the observation group.

All national SAE, SAR, and SUSARs reported in the CRF during the trial will be listed and reported yearly by the national investigator to the National Health Authority and to the National Ethics Committee according to the national regulations by the national study secretary.

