All SUSARs will be listed and reported yearly by the sponsor to the national investigators and to the Danish Health Authorities.

Annually the steering committee will discuss the numbers of SAE, SAR, and SUSARs in the two patient arms. Based on these data the committee will decide if the study should be terminated before time. Likewise an interim analysis will be conducted when half the patients have completed the study. If significant relevant different is observed already at this time-point the study will also be terminated for the benefit of the remaining patients

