**1.9.1 Definitions of which AE and SAE that are to be reported in the CRF**

In this study, all cases of BON, renal insufficiency, hypo-, and hypercalcaemia will be reported as an Adverse Event (AE) or a Serious Adverse Event (SAE). An adverse event is any new, undesirable medical occurrence or change of an existing condition, whether or not it is considered related to the treatment. A serious adverse event includes, but may not be limited to:

-Death due to study medication

-Life threatening complications

-Inpatient hospitalisation or prolongation of existing hospitalisation

-Significant and persistent disability / incapacity

-An event that may require medical or surgical intervention to prevent one of the outcomes list above

In this study, temporary renal insufficiency that can be reversed either by fluid replacement or by treatment reduction will be perceived as an AE, persistent renal insufficiency will be perceived as a SAE. Persistent grade 2 BON or any grade 3 BON will be perceived as a SAE

Renal insufficiencies, hypo-, and hypercalcaemia:

Renal insufficiency hypo-, and hypercalcaemia AEs will be graded according to the National Cancer Institute Common Toxicity Criteria for Adverse Evens (NCI CTCEA) version 4.0. All AEs should be reported and related to the study drug administration as follows:

Not related:

An adverse event, which is not related to the use of the drug.

Unlikely/doubtful:

An adverse event for which an alternative explanation is more likely, e.g., concomitant drug(s),

concomitant disease(s), or the relationship in time suggests that a causal relationship is unlikely.

Possible:

An adverse event, which might be due to the use of the drug. An alternative explanation, e.g., concomitant drug(s), concomitant disease(s), is inconclusive. The relationship in time is reasonable,therefore, the causal relationship cannot be excluded.

Probable:

An adverse event, which might be due to the use of the drug. The relationship in time is suggestive (e.g., confirmed by repetition). An alternative explanation is less likely, e.g., concomitant drug(s), concomitant disease(s).

Definitive/very likely:

An adverse event that is listed as a possible adverse reaction and cannot be reasonably explained by

an alternative explanation, e.g., concomitant drug(s), concomitant disease(s). The relationship in

time is very suggestive (e.g., it is confirmed by de-challenge and re-challenge).

BON:

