BON is a rare occurring event and should always be reported as at least possible related. If the patient has received radiation therapy to the neck or mandibular region one should keep the differential diagnosis of osteoradionecrosis in mind. If the treating clinician discovers cases of osteoradionecrosis this should still be reported as a possible case of BON.

Bon will be graded according to the 2009 AAOMS position paper on BON [[30](#_ENREF_30)].

Stage 0: No clinical evidence of necrotic bone, but nonspecific clinical findings and symptoms.

Stage 1: Exposed and necrotic bone in asymptomatic patients without evidence of infections.

Stage 2: Exposed and necrotic bone associated with infections as evidenced by pain and erythema in region of exposed bone with or without purulent drainage.

Stage 3: Exposed and necrotic bone in patients with pain, infection, and one or more of the following: exposed and necrotic bone extending beyond the region of alveolar bone, (ie, inferior border and ramus in the mandible, maxillary sinus and zygoma in the maxilla) resulting in pathologic fracture, extraoral fistula, oral antral/oral nasal communication, or osteolysis extending to the inferior border of the mandible or the sinus floor.

Exceptions to AE and SAE reporting.

Hospitalisations or prolongation of hospitalisation due to progression of MM or well-known complications to multiple myeloma e.g. infection or anaemia do not need to be reported to the study secretariat, nor must a SAE report be completed. It also applies to complications to administration of myeloma treatment, other elective measures or for social reasons. Death due to progression of multiple myeloma do not need to be reported as an SAE.

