**1.14 Ethical Considerations**

Multiple myeloma remains an incurable malignant disorder; however the average expected lifetime is increasing due to improved treatment. Treatment monthly with zoledronic acid is known to reduce the risk pathological fractures, progressive osteolysis, and to reduce pain. No knowledge exists on what should be done after two years of treatment. Prolonged treatment carries the risk of BON, whereas discontinuation of treatment probably increases the risk of PBD. The primary purpose of the study is to investigate if prolonged treatment with zoledronic acid provides adequate protection against PBD to justify an increased risk of BON. To investigate this, patients will be randomized 1:1 to receive either 2 or 4 years of treatment. To protect participating patients from both under- overtreatment, routine oral cavity examinations and bone imaging are planned in the protocol. Bone imaging is balanced between early detection of PBD (and thus possible removal from the protocol) and minimal radiation exposure. It is estimated that a patients will receive an excess radiation dose of 33.2 – 36.6 mSv equal to the dose received from 1.5 conventional CT. This radiation exposure is not ignorable. The median age of a newly diagnosed patient however is approximately 70 years, they all suffer from an incurable cancer and have a severely reduced life expectancy. This reduces the long-term risk of secondary malignancies due to radiation exposure to approximately 0.0175%. Furthermore, the additional bone imaging will not only help us decide if the more sensitive modality low-dose CT in the future should replace conventional radiography, it will also help determining if serum samples partly can replace bone imaging, thus reducing future radiation exposure. Most importantly, it will in the actual patient help us detect progressive bone disease before this becomes symptomatic due to e.g. vertebral collapse or pathological fractures.

An additional part of the study is to investigate if serum bone markers can be used to tailor treatment with zoledronic acid in the individual patients in the future. To investigate this, extra serum will be collected and stored for later analysis. This extra serum will be collected when blood samples to monitor the myeloma disease are collected anyway, thus no additional appearances at the outpatient clinic for blood draws over the course of the study are anticipated.

REGULATORY ETHICS COMPLIANCE

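### The annual steering committee review can end the trial on SAE, SAR and SUSAR counts that hold little of the harm the protocol expects from stopping zoledronic acid

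*Protocol*

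**What the plan says.** Section 1.9 sets the input to the yearly review: "Annually the steering committee will discuss the numbers of SAE, SAR, and SUSARs in the two patient arms". The next sentence ties the decision to it: "Based on these data the committee will decide if the study should be terminated before time".

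The reporting rules decide what those counts can contain:

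- Under 1.9, AEs and SAEs "will not be reported in the CRF if they can be related to the myeloma disease or to the chemotherapeutic treatment the patient receives".
- Under 1.9.1, "all cases of BON, renal insufficiency, hypo-, and hypercalcaemia will be reported as an Adverse Event (AE) or a Serious Adverse Event (SAE". Fracture, vertebral compression and new or growing lesions are not on that list.
- The exceptions in 1.9.1 release sites from reporting "Hospitalisations or prolongation of hospitalisation due to progression of MM or well-known complications to multiple myeloma". They add: "Death due to progression of multiple myeloma do not need to be reported as an SAE". The SAE criteria in the same section mention death only when the study drug caused it.
- BON is always to be classed as at least possibly related (1.9.1).

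Symptomatic bone progression has its own route in 1.8: "All cases of sPBD will be reported annually to the sponsor". That sentence mentions neither the steering committee nor a comparison of arms.

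Section 1.14 names the trade-off that the trial is meant to weigh: "Prolonged treatment carries the risk of BON, whereas discontinuation of treatment probably increases the risk of PBD".

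**The concern.** The protocol expects one main harm in each arm: BON from continuing (arm B) and PBD from stopping (arm A). A yearly decision on whether to go on should see both. As written, the counts take in the first and leave most of the second outside.

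This is not a detail left for a later document, because 1.9 itself fixes the data on which the decision rests. If the text is followed, the annual review could end the trial for an excess of drug reactions in arm B without seeing the bone events that continued treatment may have prevented. An excess of fractures or myeloma deaths in arm A would not show in its table.

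**Working it through.** **Step 1. Which events reach the annual counts**

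| Event | In the SAE/SAR/SUSAR counts? | Source |
|---|---|---|
| BON | Yes. Always at least possibly related; persistent grade 2 or any grade 3 is an SAE | 1.9.1 |
| Renal insufficiency | Yes when persistent (SAE), whatever the cause | 1.9, 1.9.1 |
| Hypo- or hypercalcaemia | Yes when serious, whatever the cause; hypercalcaemia is also a component of PBD and sPBD | 1.5, 1.9, 1.9.1 |
| Other serious drug reactions | Yes | 1.9, 1.9.2 |
| Fracture, vertebral compression, new or growing lesions | No. Not listed, and kept out when attributed to the myeloma | 1.9, 1.9.1 |
| Hospitalisation for myeloma progression | No | 1.9.1 |
| Death from myeloma | No | 1.9.1 |
| sPBD as such | Goes to the sponsor yearly; not named as an input to the decision | 1.8 |

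Arm A receives no drug after year 2. By inference, new drug reactions arise mainly in arm B, apart from late BON in arm A. The protocol gives no figure for this.

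**Step 2. The planning figures**

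Inputs from 1.13: 143 per group, 7.5% PBD a year on drug, a ratio of 0.5, one-sided 0.05, 80% power and two years. The ratio is read here as 15% a year off drug.

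- Events (Freedman): (1.645 + 0.842)² × (1.5/0.5)² = 6.18 × 9 = 55.6, so 56.
- Two-year event probabilities with constant hazards: 1 − exp(−0.15) = 0.139 and 1 − exp(−0.30) = 0.259.
- Size per group: 56 / (0.1393 + 0.2592) = 140.5, so 141. This is close to the stated 143 and consistent with the 15% reading.
- Inclusion: 286 / 0.8 = 357.5, so 358, as stated.

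**Step 3. How many events a year are at issue**

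Section 1.20 has initiation at the end of 2014, inclusion to 01.12.2020 and two years of follow-up. The pace of randomisation is not given. I assume it is uniform, over 6 years (amendment patients are randomised at entry) or over 4 years (original patients reach randomisation only from late 2016). Losses are ignored.

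- At risk per arm at one time: 143 × 2/6 = 47.7, or 143 × 2/4 = 71.5.
- PBD excess in arm A: 47.7 × (0.15 − 0.075) = 3.6, or 71.5 × 0.075 = 5.4 a year.
- sPBD excess, with 5% on drug (1.13) and an assumed 10% off drug: 47.7 × 0.05 = 2.4, or 71.5 × 0.05 = 3.6 a year.

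The share of these that is serious hypercalcaemia, and so visible to the review, is not given.

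**Step 4. Sensitivity**

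Section 1.13 expects 32 PBD cases over years two to four. At these rates that is one year's worth: 143 × (0.075 + 0.15) = 32.2. If 32 were the true two-year total, the yearly PBD excess would halve to about 1.8 to 2.7. The direction of the gap would not change.

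**The case against.** The strongest case against is that the annual review is only one of several safeguards.

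- Section 1.9 also plans an interim analysis when half the patients have completed, with termination if a relevant difference is seen. Its endpoint is not named, but time to PBD is primary, so it most naturally covers PBD. Section 1.20 plans a further look at the end of inclusion that explicitly weighs PBD against BON.
- Scheduled imaging in 1.7, and imaging at relapse, protect the individual patient.
- sPBD goes to the sponsor yearly, just as BON does (1.8). The pages at hand do not show whether the sponsor sits on the steering committee.
- Arm A is not invisible. Late BON, renal insufficiency and calcium events are recorded there too, up to year 4 plus 30 days.
- Keeping disease progression out of SAE counts and judging it at interim analyses is a recognised design.

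Most of this stands, and it sets the limits of the point. A reader might infer that the trial as a whole can be stopped early only for harm in arm B. The documents do not support that, because both interim analyses can also end the trial and one of them names PBD.

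A reader might also multiply 143 by 7.5 percentage points and report about 11 excess PBD cases a year (143 × 0.075 = 10.7). That needs all 143 per arm at risk in the same year, which staggered entry rules out.

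What the objection does not answer is the annual decision itself. Imaging protects single patients but does not show a committee that one arm is doing worse. The look in 1.20 happens once, about six years after the planned start. No sentence brings PBD, sPBD or deaths by arm into the yearly review.

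**Conclusion.** The point holds for the annual review in 1.9 and no further. The protocol rests a yearly termination decision on counts that capture BON and drug reactions but, by its own reporting rules, little of the harm it expects from stopping.

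The size is moderate: about 4 to 5 excess PBD cases a year in arm A, or about 2 to 4 sPBD cases, of which only serious hypercalcaemia would be counted. These figures rest on 15% PBD and 10% sPBD a year off drug, uniform randomisation over 4 to 6 years, and no losses. Myeloma deaths are left out as well; no rate is given from which to size them.

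The interim analyses and the imaging lessen the consequence but do not repair the yearly review.

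**What to change.** In 1.9, add three items to the annual review as safety inputs, by randomised arm with patients and person-time: the sPBD cases that 1.8 already sends to the sponsor each year, deaths from any cause, and BON by stage. Deaths are already in the CRF as a reason for leaving the study (1.12). Base the yearly decision on this table together with the SAE, SAR and SUSAR counts, and say in 1.8 that the sPBD reports also go to the committee by arm.

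Leave the comparison of time to PBD to the planned interim analyses. If PBD by arm is also shown yearly, state that it serves stopping for harm only and not a claim of efficacy. Otherwise the one-sided 0.05 test gains repeated unadjusted looks. Because sPBD is part of PBD, the same statement should cover it.

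The cost is one more table a year. Deaths after exclusion may be incomplete, since 1.6 plans no further protocol follow-up once a patient leaves and 1.12 only 30 days for adverse events. The committee of an open trial would also see more outcome data by arm than it does now.

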**1.13 Statistical Considerations.**

Primary endpoint:

There are no published data on the incidence on PBD from year 2 and onward in MM. However, there are data showing the annual incidence of the more strict sPBD is approximately 5% in patients receiving continuous zoledronic acid [[31](#_ENREF_31)]. Since we in this study use a less strict definition of progression in bone disease, we assume the annual incidence will be 7.5% instead of only 5% in patients receiving zoledronic acid. Based on data from the MRC IX trial and from an ASH publication in 2012 we expect to see risk reduction rate of 0.5 [[32](#_ENREF_32)]. With a significance threshold of 0.05, one-sided, a power of 80, and a fixed study duration of 2 years, we need a sample size of 143 per group to detect a difference in the primary endpoint. 286 patients in total need to be allocated to the two treatment arms. However, due to the nature of the disease, 30% of all patients will be dead before year two. Due to the in- and exclusion criteria we presume that only 20% of the study population will be dead before stratification. Thus 358 patients in total need to be included in the protocol. Data will be analysed according to the treatment the patients actually received using the Kaplan-Meier analysis. Patients will be analysed per protocol. New data have shown significant reduction in PBD after 4 years treatment with zoledronic acid compared to 2 years of treatment in 170 randomised patients^33^.

Other endpoints:

Serum samples will be collected and stored from all patients. From the calculations above, we expect 32 cases of PBD during year two to four. Bone markers will be measured on these patients from the time of PBD and 6 month prior to the bone event. An equal number of controls will be selected as the number of cases PBD actually observed and bone markers will be measured likewise in these patients. The controls will be selected according the stratification criteria’s (previous autologous stem cell treatment, presence or absence of bone disease at diagnosis, and previous treatment with bortezomib). If multiple options are present the same gender will be chosen, and after that the closest age related. Data will be analyzed as a case control study

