**1.20 Timescale**

Initiation is expected to occur end 2014, and due to new data inclusion will end 01.12.2020 with a follow up two years the expected termination date is 01.12.2022.

An interim analysis will be conducted at the end in inclusion. The steering committee will then decide if the positive effect of a decrease in the number of PBD outweighs a negative effect of an increased risk of BON, or if the study should be terminated.

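### The interim analysis has two unreconciled triggers and a mandatory stop with no endpoint, level or boundary, so the protocol as written does not keep its one-sided 5% error rate

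*Protocol*

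**What the plan says.** Section 1.9 (Side Effects) describes the annual safety review by the steering committee and then continues: "Likewise an interim analysis will be conducted when half the patients have completed the study". The consequence follows directly: "If significant relevant different is observed already at this time-point the study will also be terminated for the benefit of the remaining patients". No endpoint, significance level or boundary is attached, and the relevance that the difference must have is not defined.

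Section 1.20 (Timescale) says: "An interim analysis will be conducted at the end in inclusion". There the steering committee weighs fewer PBD events against a higher risk of osteonecrosis of the jaw (BON) and decides whether to go on. No statistical criterion is given. Neither section refers to the other.

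Section 1.13 (Statistical Considerations) sets the error rate: "With a significance threshold of 0.05, one-sided, a power of 80, and a fixed study duration of 2 years". It then states: "we need a sample size of 143 per group to detect a difference in the primary endpoint". It does not mention an interim look or an adjusted final level.

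**The concern.** There are two problems.

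First, a reader cannot tell from 1.9 and 1.20 whether one look or two is planned, when it happens, or which rule governs it. One section makes termination follow from a test result; the other leaves it to a benefit-risk judgement.

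Second, the only significance level anywhere in the protocol is the one-sided 0.05 in 1.13, and that is the whole of the final level. If a mandatory stop on significance uses the same level, the trial has two chances of a false positive at 0.05 each, and the overall error exceeds 5%. A trial stopped because it crossed so low a bar would also tend to overstate the benefit of continuing zoledronic acid. That benefit is one side of the PBD-against-BON balance the trial is meant to settle.

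**Working it through.** **1. Does the sample size allow for an interim look?** Inputs from 1.13: one-sided alpha 0.05, power 80%, two years; "we assume the annual incidence will be 7.5% instead of only 5% in patients receiving zoledronic acid"; "we expect to see risk reduction rate of 0.5", read as a hazard ratio of 0.5, so 15% per year after stopping.

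- Events (Freedman, single look): (1.645 + 0.842)² × [(1 + 0.5)/(1 − 0.5)]² = 6.18 × 9 = 55.6, so 56.
- Two-year event probabilities (exponential): 1 − exp(−0.15) = 0.139 and 1 − exp(−0.30) = 0.259; sum 0.398.
- Patients per group: 56/0.398 = 141, against 143 stated (within 3%).
- Inclusion: 286/0.80 = 357.5, so 358, exactly as stated.

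The figures match a single-look design with nothing set aside for an interim.

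**2. What information fraction do the triggers imply?** The protocol gives none, so this is an assumption. Section 1.20 starts the trial at the end of 2014 and closes inclusion on 01.12.2020, with two years of follow-up. Patients on the original route are randomised two years after entry, so from about the end of 2016. Patients entering under the amendment go straight to randomisation and could be earlier. That suggests a randomisation window A of 4 to 6 years. I assume uniform randomisation, a constant event rate and two years of follow-up per patient. Information is then approximately follow-up accrued divided by total follow-up (2A, per patient randomised per year).

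- Half completed falls at A/2 + 2 years. For A = 4 this is year 4: (2×2 + 2)/8 = 0.75. For A = 6 it is year 5: (3×2 + 2)/12 = 0.67.
- End of inclusion falls at A years. For A = 4: (2×2 + 2)/8 = 0.75. For A = 6: (4×2 + 2)/12 = 0.83.

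Both triggers therefore lie at about 0.67 to 0.83. With A = 4 they fall on the same date.

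**3. Error rate if 0.05 is used twice.** With information fraction t, the interim and final statistics are bivariate normal with correlation √t under the null. Overall one-sided error = 1 − P(Z1 < 1.645 and Z2 < 1.645).

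| t | Overall one-sided error |
|---|---|
| 0.50 | 8.0% |
| 0.67 | 7.4% |
| 0.75 | 7.1% |
| 0.83 | 6.7% |

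If the interim instead used two-sided 0.05 (upper tail 0.025) and the final one-sided 0.05, the error at t = 0.5 would be 6.2%.

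**4. Boundaries that restore 5%.**

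- Classical O'Brien-Fleming at t = 0.5: interim p < 0.0088, final p < 0.0467 (one-sided). Sample size factor 1.016; power with the size unchanged is 79.5% instead of 80%.
- Lan-DeMets O'Brien-Fleming-type spending, α(t) = 2[1 − Φ(1.96/√t)]: at t = 0.5, interim p < 0.0056 and final p < 0.0482. At t = 0.75, 1.96/0.866 = 2.263, so interim p < 0.0236, and solving for an overall 5% gives final p < 0.0431.
- Interim p < 0.001 with the final left at 0.05: overall 0.0502 at t = 0.5.

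**5. Planned number of events.** Section 1.13 expects 32 PBD cases, which equals 143 × (0.15 + 0.075) = 32.2. The rates that reproduce 143 per group give 143 × 0.398 = 57. Half the planned events is therefore 16 or about 28, depending on which figure is used.

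**The case against.** The strongest objection is that nothing in 1.9 sets the interim level at 0.05. The paragraph sits under Side Effects, follows the safety review and names no endpoint. A stop on safety alone would not inflate the error for PBD. The difference must also be relevant, which is more than a bare test, and numerical boundaries are often left to a statistical analysis plan, which may exist.

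Part of this stands: the inflation is conditional on a PBD test at 0.05. But an undefined relevance condition is not shown to control any error. The interim in 1.20 explicitly considers PBD. And the protocol does more than leave a gap: it fixes a mandatory stop, two timings and a single unadjusted level.

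Three stronger readings are tempting and are not supported:

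- **Two extra looks, with an error of 9% to 10%.** This counts the review in 1.20 as a second test at 0.05, but that section describes a judgement and no test.
- **8.0% as the main figure.** It needs exactly half the information. When half the patients have completed, the others have contributed follow-up too, so the fraction is probably higher and the inflation smaller.
- **Triggers that must fall on different dates.** With uniform randomisation over four years they coincide. The wording conflicts; a conflict in calendar time is not established.

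**Conclusion.** The point holds in a conditional form. Sections 1.9 and 1.20 give different triggers and different decision rules for an interim analysis. Section 1.9 makes termination mandatory without stating endpoint, level or boundary, and 1.13 makes no allowance for a look.

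If the interim tests PBD at the only level the protocol offers and the final test repeats it, the overall one-sided error is about 6.7% to 7.4%, not 5%. This rests on one interim look, uniform randomisation over 4 to 6 years and a constant event rate. At 50% information it would be 8.0%. The inflation is moderate, but it affects the confirmatory error rate and is cheap to remove.

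**What to change.** - State the same single interim trigger in 1.9 and 1.20, or declare openly that two looks are planned and control the error over both.
- Name PBD as the endpoint of the efficacy test.
- State in 1.13 an efficacy boundary that keeps the overall one-sided 5%, with the matching final level. A Lan-DeMets O'Brien-Fleming-type function evaluated at the actual information fraction suits a trigger whose information is uncertain. An interim p < 0.001 with the final at 0.05 is a simpler alternative.
- If the trigger is to be event-based, first reconcile the 32 expected PBD cases with the roughly 57 implied by the sample size.
- Say how the steering committee's weighing of PBD against BON relates to the boundary, without removing its ability to stop for safety.

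The cost is protocol wording. Stopping early for efficacy becomes harder. Power with 286 randomised falls by about half a percentage point under classical O'Brien-Fleming at 50% information, or the sample size rises by 1.6% (286 × 0.016, about 5 patients) to hold it. Lan-DeMets spending at 0.67 to 0.83 costs about one percentage point at most.
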